# Transversus abdominis plane block following abdominally based breast reconstruction: study protocol for a randomized controlled trial

**DOI:** 10.1186/1745-6215-14-424

**Published:** 2013-12-10

**Keywords:** Autologous abdominal tissue, Breast reconstruction, Donor site, Local pain block, Transversus abdominis plane catheter

## Abstract

**Background:**

Breast reconstruction using the free muscle-sparing transversus abdominus myocutaneous or deep inferior epigastric perforator flaps are common methods for restoring mastectomy defects for breast cancer patients. Despite its increasing popularity and safety, the abdominal donor site remains a major source of postoperative pain. Conventional postoperative pain relief protocol consists primarily of a patient-controlled anesthesia device delivering intravenous opioids. Opioids can cause numerous side effects such as sedation, headache, nausea, vomiting, breathing difficulties and bladder and bowel dysfunction. A promising approach to provide postoperative pain control of the abdominal incision is the newly developed transversus abdominis plane peripheral nerve block.

**Methods/Design:**

This study is a double-blind, placebo-controlled, randomized controlled trial designed to rigorously test the effectiveness of a transversus abdominis plane catheter delivering intermittent local anesthetic in reducing postoperative abdominal pain following abdominal tissue breast reconstruction. The primary objective of this study is compare the mean total opioid consumption in the first postoperative 48 hours between the control and study groups including the patient-controlled anesthesia amounts and oral narcotic doses converted to intravenous morphine equivalent units. The secondary outcome measures include the following parameters: total in-hospital cumulative opioid consumption; daily patient-reported pain scores; total in-hospital cumulative anti-nausea consumption; nausea and sedation scores; and Quality of Recovery score; time to first bowel movement, ambulation, and duration of hospital stay.

**Discussion:**

Autologous breast reconstruction using abdominal tissue is rapidly becoming the reconstructive option of choice for postmastectomy patients across North America. A substantial component of the pain experienced by patients after this abdominally based procedure is derived from the abdominal wall incision. By potentially decreasing the need for systemic opioids and their associated side effects, this transversus abdominis plane block study will utilize the most scientifically rigorous double-blind, placebo-controlled, randomized controlled trial methodology to potentially improve both clinical care and health outcomes in breast cancer surgery patients.

**Trial registration:**

Clinicaltrials.gov NCT01398982

## Background

Autologous breast reconstruction using abdominal tissue is rapidly becoming the reconstructive option of choice for postmastectomy patients across North America. A substantial component of the pain experienced by patients after abdominally-based autologous tissue breast reconstruction is derived from the abdominal wall incision [1-3]. The conventional postoperative analgesic regimen following abdominally based autologous tissue breast reconstruction still primarily utilizes systemic opioids, which can cause sedation, headache, nausea, vomiting, respiratory compromise, pruritus and bladder and bowel dysfunction [4,5].

It is well-known that adequate analgesia decreases the incidence of cardiopulmonary complications and in-hospital deaths [6]. Several authors have investigated methods of improving postoperative analgesia with the use of a local anaesthetic (LA) infusion catheter in the donor site following abdominal flap reconstruction of the breast [7-11]. To date, the results have been mixed in these studies aimed at decreasing pain in the donor site following free muscle-sparing transversus abdominus myocutaneous (MS-TRAM) flaps or deep inferior epigastric perforator (DIEP) flaps [12-16]. The use of peripheral nerve blocks has become increasingly popular over the past two decades. With the use of anatomical landmark-based techniques, novel types of nerve blocks have been designed to deliver effective and directed analgesia. The transversus abdominis plane (TAP) block is a newly developed block involving the T6-L1 intercostal nerves, which supply the anterior abdominal wall [17-20]. In the TAP block, the lumbar triangle of Petit is used as a landmark for injecting LA into the neurovascular plane of the abdominal wall (the TAP plane) between the internal oblique and transversus abdominis muscle layers [17]. The triangle of Petit is configured with the iliac crest forming the base, the external oblique muscle being the anterior border and the latissimus dorsi muscle being the posterior border of the triangle. The floor of the triangle is made up of superficial fascia covering the transversus abdominis muscle. Both the blind TAP block and ultrasound-guided TAP block have been associated with minimal complications [7,8,11-13,15]. Recent published clinical trials involving patients who have undergone major abdominal and gynaecological surgery have demonstrated promising results with the use of this technique as part of multimodal postoperative pain treatment [7,8,10,21-24].

Our group recently published the results of a prospective cohort study that compared the total intravenous *patient-controlled analgesia* (PCA) opioid consumption between a group of 45 consecutive patients who received intermittent postoperative bolus injections of 0.25% bupivacaine through the TAP catheter and a group of 80 historic control patients who underwent the same abdominally based microsurgical breast reconstruction without TAP blocks [25]. We found that the 48-hour PCA-delivered opioid requirement was significantly less (*P* < 0.001) in the TAP block group (17.10 ± 17.23 mg intravenous morphine equivalent) compared to the control group (48.44 ± 39.53 mg). Although we concluded on the basis of data derived from our study that intermittent delivery of bupivacaine through the TAP block significantly reduced postoperative parenteral opioid requirements following abdominally based breast reconstruction, there are inherent biases associated with using historic controls. Therefore, we designed our present double-blind, placebo-controlled, randomized controlled trial (RCT) to rigorously assess the efficacy of reducing postoperative donor site pain by intermittently delivering a LA agent through the TAP catheter in patients undergoing breast reconstruction using abdominal tissue microsurgical reconstruction.

## Methods

### Study design

This double-blind, placebo-controlled RCT is a two-group parallel superiority trial. Figure 1 provides an overview of the trial design. Institutional research ethics board approval was obtained from the University Health Network (REB 10-0969-A). The source population will be members of the mastectomy cohort identified from the Breast Reconstruction Clinic at Toronto General Hospital by the two participating plastic surgeons (TZ and [name]). Potential research participants will be reviewed by a research coordinator, who will determine the suitability of each patient by reviewing her medical records (see Eligibility). Full written informed consent will be obtained from each participant by the research coordinator.

**Figure 1 F1:**
[figure not shown]
**Transversus abdominis plane trial design chart.** BMI, body mass index.

### Randomization

Once informed consent is obtained from the patient to participate in this trial, the research assistant will contact the study pharmacist to obtain the patient’s randomization arm. Patients will be randomized to receive either bupivacaine (study group) or isotonic saline (control group) through the TAP catheter by intermittent injection. The randomization allocation list will be developed by the Department of Epidemiology and Biostatistics at the University Health Network Research Institute. Randomization allocation will be equal between the study groups and stratified by laterality of abdominal flap harvest (unilateral vs. bilateral) and the timing of breast reconstruction (at the same time as mastectomy (immediate) vs. at a later time, after the mastectomy (delayed)). Sequentially numbered and sealed envelopes containing the treatment assignments will be prepared and given to the study pharmacist. The patient, surgeon, research assistant and all other study personnel will be blinded to randomization. The randomization code will be revealed only after the completion of the trial and all the patient data have been collected.

### Eligibility

The following are the inclusion criteria. (1) Patients must be older than 18 years of age, with no upper age limit. (2) Participants must be able to speak English. (3) Treatment must be immediate or delayed microsurgical breast reconstruction using abdominal tissues (free MS-TRAM or DIEP flap).

The following are the exclusion criteria: (1) patient refusal; (2) inability to give informed consent; (3) body mass index (BMI) greater than 40; (4) allergy to bupivacaine; (5) patients who will undergo implant breast reconstruction or non–abdominally based autologous tissue reconstruction; (6) any drug addiction; (7) opioid tolerance, defined as preoperative daily opioid use higher than 50 mg of a morphine equivalent by mouth (in the previous 2 months); and (8) any psychiatric illness, excluding depression and anxiety.

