### Primary end point and secondary end points

The primary end point evaluated will be the mean postoperative opioid consumption in the first 2 postoperative days. Both intravenous PCA opioids and oral opioids will be recorded from the patients’ medical records daily. All opioid doses will be converted to intravenous morphine equivalent units for comparison.

The secondary outcomes of interest will include the following. The continuous outcomes will be total in-hospital cumulative opioid consumption, total in-hospital cumulative antinausea medication consumption, score on the Quality of Recovery (QoR) questionnaire administered once on postoperative day 4 (scored from 0 to 18, with a greater score indicating better QoR) [9] and duration of hospital stay. Therepeated-measures outcomes will be assessed by recording daily pain intensity scores at rest and with movement measured using a Visual Analogue Scale for pain (scored from 0 to 10, with 0 indicating no pain and 10 indicating worst pain ever), postoperative nausea and vomiting (scored from 0 to 3) and sedation score. The time to event outcomes will be recorded for time to first postoperative bowel movement and time to ambulation.

The data extraction forms will be completed prospectively by a member of the pain team.

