### Data analysis

Patients who have major postoperative complications that require a second surgery, such as evacuation of a hematoma or microsurgical revision, will not be removed from the study and will be evaluated using the intention-to-treat analysis. An initial examination will be performed to detect any differences between the two treatment groups despite the randomization. Patients’ clinical, surgical and oncological characteristics, such as BMI and method of reconstruction (DIEP or MS-TRAM) will be collected and their association with the primary and secondary outcomes will be tested in univariate analysis models to detect possible confounding factors. The effect of treatment groups will be studied next using an appropriate multivariate analysis model for each outcome while controlling for the possible confounding factors, if indicated, such as BMI and method of reconstruction. All statistical analyses will be performed using SAS software version 9.2 (SAS Inc, Cary, NC, USA). All tests will be two-sided, and significance will be set at *P* < 0.05.

The primary analysis will comprise mean postoperative opioid consumption during the first 48 hours postoperatively, which will be reported for the two groups as means (±SD). The two groups will be compared using the two-sample Student’s *t*-test or the Wilcoxon rank-sum test, depending on the results of the normality test. The secondary analysis will assess continuous outcomes, which will be reported for the two groups as means (±SD). The median and range will also be reported. The two groups will be compared using the two-sample Student’s *t*-test or the Wilcoxon rank-sum test, depending on the normality test.

Repeated-measures outcomes will be analysed to assess the effect of treatment (between-subject variable), time (within-subject variable) and a possible treatment × time interaction on outcomes measured at various time points. Time-to-event outcomes will be measured from the completion of surgery until the time of the event. Patients who do not experience the event at the time of the last follow-up will be censored. The number of censored events is expected to be low because both events (ambulation and bowel movement) are required to occur prior to the patient’s discharge from the hospital. Time-to-event outcomes will be analysed using the Kaplan-Meier method, and survival curves will be compared between the two groups using the logrank test.

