### Sample size calculations

A retrospective review of 45 patients matched on key characteristics that underwent free MS-TRAM or DIEP breast reconstruction between January 2009 and March 2010 prior to the use of TAP block revealed a mean total opioid consumption of 9.2 mg ± 5.8 mg of intravenous morphine equivalent per patient. Using these preliminary data, we will require 29 patients per group to achieve 80% power to detect a 50% reduction in mean total opioid consumption between the control and study groups (9.2 vs. 4.6 mg, respectively) with group standard deviations of 5.8 mg and a significance level (Cronbach’s α) of 0.05 using a two-sided Wilcoxon rank-sum test assuming that the actual distribution is normal. From January to December 2010, approximately 100 patients underwent microsurgical breast reconstruction using abdominal tissue performed by the two participating surgeons (TZ and [name]). It is anticipated that approximately 80% of these patients will be eligible and willing to participate in the study (approximately six or seven patients per month). A total of 58 patients will be enrolled into this proposed study, thus the estimated accrual time is approximately 9 to 12 months.

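### The primary comparison leaves out preoperative opioid use (allowed up to 50 mg/day orally) and both stratification factors, giving up precision but not validity

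*Protocol article*

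**What the plan says.** **Eligibility.** Exclusion criterion 7 defines opioid tolerance as "preoperative daily opioid use higher than 50 mg of a morphine equivalent by mouth (in the previous 2 months". Anyone at or below that level can enter. The Study design section has a research coordinator judge suitability from the medical records.

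**Outcome.** "The primary end point evaluated will be the mean postoperative opioid consumption in the first 2 postoperative days". PCA and oral opioids both count, and all are converted to intravenous morphine equivalents.

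**Randomisation.** "Randomization allocation will be equal between the study groups", and allocation is "stratified by laterality of abdominal flap harvest (unilateral vs. bilateral) and the timing of breast reconstruction". Opioid history is not a stratification factor.

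**Analysis.** The Data analysis section compares the groups on the primary outcome with a two-sample t-test "or the Wilcoxon rank-sum test, depending on the results of the normality test". Separately, patient characteristics are screened one at a time against the outcomes. A multivariate model then follows, "controlling for the possible confounding factors, if indicated, such as BMI and method of reconstruction". Neither the stratification factors nor preoperative opioid use is named for any model.

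**The concern.** Preoperative opioid use is the baseline counterpart of the primary outcome. A patient who takes opioids daily before surgery may need some of that amount afterwards whether or not the block works, and it would be counted in the 48-hour total. With a few dozen patients per arm, chance can place more such patients in one arm, and the planned primary test does nothing to offset this. Laterality and timing were thought important enough to stratify on, yet the primary test leaves them out as well.

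The planned adjusted model is a weak safeguard. Its covariates depend on screening against the outcome data. A variable that is non-zero in only a few patients can easily fail such a screen, and one admitted that way has not been prespecified.

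**Working it through.** **1. The plan's own figure.** Sample size calculations: "we will require 29 patients per group to achieve 80% power to detect a 50% reduction in mean total opioid consumption", 9.2 against 4.6 mg, SD 5.8 mg, tested at "0.05 using a two-sided Wilcoxon rank-sum test assuming that the actual distribution is normal". A two-sample t-test needs 25.95 per group. Dividing by the rank-sum efficiency under normality, 3/π, gives 25.95 × π/3 = 27.2, so 28. Simulated rank-sum power at 29 per group is about 82%. The stated 29 is therefore adequate for its inputs, and this point does not rest on a sample size error.

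**2. Gain from adjustment, by correlation.** Let ρ be the correlation of the baseline variable with the outcome. The document gives no value, so a range is assumed. The residual SD is 5.8 × √(1 − ρ²).

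| ρ (assumed) | Variance removed | Power at 29 per group, t-test basis |
|---|---|---|
| 0 | 0% | 84.3% |
| 0.1 | 1% | 84.7% |
| 0.3 | 9% | 87.5% |
| 0.5 | 25% | 92.9% |

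**3. Typical chance imbalance.** With 29 per arm, the between-arm difference in a baseline variable has standard deviation √(2/29) = 0.26 baseline SDs. A one-SD imbalance moves the unadjusted treatment difference by ρ × 5.8 × 0.26. That is 0.46 mg at ρ = 0.3 and 0.76 mg at ρ = 0.5, or 10% to 17% of the 4.6 mg target.

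**4. Worst single patient.** Assumptions: oral-to-intravenous ratio 3:1 (alternative 2:1; the document gives none), use at the 50 mg ceiling, and full replacement over 48 hours. Then 50 ÷ 3 × 2 days = 33.3 mg, or 50 ÷ 2 × 2 = 50 mg. One extra such patient in an arm of 29 shifts the difference in means by 33.3/29 = 1.15 mg to 50/29 = 1.72 mg, which is 25% to 37% of 4.6 mg. Trial status reports 86 enrolled. At 43 per arm, assuming an equal split, the shift is 0.78 to 1.16 mg (17% to 25%).

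**5. Variance explained, by assumed prevalence.** Let a proportion p be users, with intravenous-equivalent need spread evenly from 0 to m. The added variance is p·m²/3 − (p·m/2)².

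| p | m (mg) | Added variance (mg²) | Share if the rest has SD 5.8 | Share if the rest has SD 39.53 |
|---|---|---|---|---|
| 5% | 33.3 | 17.8 | 35% | 1.1% |
| 10% | 33.3 | 34.3 | 50% | 2.1% |
| 5% | 50 | 40.1 | 54% | 2.5% |
| 10% | 50 | 77.1 | 70% | 4.7% |

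The SD of 39.53 mg is that of the historic control group's 48-hour PCA consumption, reported in the Background.

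**6. Limit on the SD 5.8 column.** The 5.8 mg is the SD observed across 45 earlier patients, so it is already a total, with variance 33.6 mg². Three of the four added variances exceed that total. If those 45 patients resemble the trial's, users were rarer than assumed or replaced less of their dose, so this column is an upper bound.

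**7. What the rank-sum branch absorbs.** Normal data were simulated at 29 per arm, with one bupivacaine-arm patient raised by 33.3 or 50 mg. Rank-sum power fell from about 82% to 71% or 72%. T-test power fell from about 84% to 41% or 13%. A Shapiro-Wilk test rejected normality in that arm in more than 90% of runs, so the plan would usually have moved to the rank-sum test.

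**The case against.** The strongest reply is that nothing here is an error. An unadjusted test in a randomised trial is valid, and its standard error already allows for chance imbalance. That stands. A reader might infer from the single-patient figures that the primary result would be biased or its type I error inflated; the design does not support that reading.

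A reader might also infer that every patient's daily dose is on file. The criterion is a threshold: a coordinator needs to establish only that use does not exceed 50 mg/day. Some knowledge of prior use must exist, but an exact dose need not.

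The 25% to 37% shift is also tempting to quote as the size of the problem. It needs a patient at the ceiling, full replacement and a comparison of means, and the rank-sum branch absorbs much of such an outlier. On the earlier cohort's difference of 48.44 − 17.10 = 31.34 mg, the same patient shifts the result by only 3.7% to 5.5%.

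Finally, the covariate list is open-ended, and covariates are often left to an analysis plan that is not shown here. This stands only in part. The article does state the primary test and the rule for choosing covariates. Under that rule preoperative opioid use may be admitted but need not be, and the choice depends on outcome data.

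**Conclusion.** The point holds as a matter of efficiency. The stated primary comparison ignores a plausibly prognostic variable fixed before randomisation, as well as both stratification factors, and the plan's only route to adjustment is data-driven. Validity is not in question.

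The size of the loss cannot be determined from the document, which gives neither the prevalence of preoperative use nor its correlation with the outcome. At an assumed prevalence of 5% to 10%, with doses spread evenly to the ceiling and fully replaced, the covariate explains about 1% to 5% of variance on the earlier cohort's SD. On the planning SD the same assumptions give 35% to 70%, an upper bound because they add user variance to an SD that is already a total. If few enrolled patients use opioids, the gain is small. The change is still worth making because it costs so little.

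**What to change.** Before unblinding, prespecify one primary model of 48-hour opioid consumption that includes treatment, laterality, timing and preoperative opioid use, whatever the univariate screening shows. ANCOVA on a suitable scale would serve, with rank ANCOVA as its stated counterpart if the data are non-normal, so that the rank-based branch is adjusted too.

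Fix the form of the opioid covariate in advance: any versus none from the screening records, or daily dose if a dose is recorded for all patients. Make that choice from what was recorded, without reference to outcomes or to how many users there turn out to be. Keep the unadjusted test as a sensitivity analysis.

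The cost is a sentence or two in the analysis section, transfer of one screening value per patient, and three degrees of freedom (one for each covariate). The Randomization section keeps the code concealed until all data are collected, so the change can be made blind.

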### Intervention plan

#### Surgical technique: insertion of the transversus abdominus plane catheter

The abdominal flaps will be harvested in a standardised manner with preservation of nerves in all cases. In both groups, the plastic surgeon will close the rectus fascia following free DIEP or MS-TRAM harvest in the routine fashion. If a synthetic mesh is required for abdominal closure, the patient will be excluded from the study. The lumbar triangle of Petit will be located by identifying its borders between the latissimus dorsi muscle posteriorly, the external oblique muscle anteriorly and the iliac crest inferiorly. (Figure 2) A 2-cm incision will be made through the abdominal fascia in the triangle of Petit. The catheter will be inserted through a stab incision 5 cm above the lateral edge of the abdominal incision. This catheter will be introduced into the TAP incision and advanced into the transversus abdominis fascial plane. The fascial defect in the triangle of Petit will be repaired using a Polysorb 0 suture (Covidien, Mansfield, MA, USA). The catheter is secured to the skin using OpSite Flexigrid tape (Smith & Nephew, St Petersburg, FL, USA) to prevent accidental dislodgement. In both unilateral and bilateral cases, two catheters will be inserted, one on each side.

